## Abstract

**Background:** Rheumatoid arthritis (RA) is a chronic inflammatory disease characterized by autoantibody production and synovial membrane damage. It significantly impairs overall function and quality of life. Consumption of omega-3 (n-3) polyunsaturated fatty acids (PUFAs) and regular aerobic exercise (AEx) training are reported to have positive effects on the progression of RA. However, the mechanisms behind these benefits are still inconclusive. This study protocol will investigate the effects of n-3 PUFA supplementation and AEx training on disease progression, cardiometabolic health, and quality of life, and their association with the plasma and synovial fluid levels of specialized pro-resolving mediators (SPMs) in subjects with RA.

**Methods:** The study consists of a 16-week intervention period, during which participants will be randomly assigned in a double-blinded manner to one of four groups: placebo control (PLA), PLA+AEx, n-3, or n-3+AEx. The PLA groups will be given a gelatin-filled capsule, while the n-3 groups will be given n-3 PUFAs equivalent to 2.5 g/d of docosahexaenoic acid and 0.5 g/d of eicosapentaenoic acid. The AEx groups will perform exercise three times per week on a stationary electronically braked cycle ergometer at 60-70% of their VO2peak for 50-60 minutes. Before and after the intervention, participants will undergo RA-specific and functional measurements, peak aerobic capacity test, and a dietary and physical activity assessment. Venous blood and synovial fluid from the knee joint will be collected. Changes in disease progression, cardiometabolic health, and quality of life, as well as erythrocyte membrane composition to assess n-3 incorporation, SPM levels, inflammatory markers, and gene expression from blood and synovial fluid will be analyzed.

**Conclusions:** The study aims to elucidate the SPMs that regulate the inflammatory gene expression pathways and associate them with the improvements in disease progression, cardiometabolic health, and quality of life after n-3 PUFA supplementation and AEx training.

**Registration**: ClinicalTrials.gov
#NCT05945693.

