^ has initiated a promising new era of research that could explain the benefits observed after n-3 PUFA supplementation and AEx in individuals with RA. However, whether they are responsible for this adaptive response, also remains to be elucidated.

*Research hypothesis:* N-3 PUFA and AEx will have synergistic effects on disease progression, cardiometabolic health, and quality of life in individuals with RA, and these changes will be associated with SPM production in blood and synovial fluid.

*General aim:* To investigate the effects of n-3 PUFA supplementation and AEx training on disease progression, cardiometabolic health, and quality of life and their association with the plasma and synovial fluid levels of SPMs in individuals with RA.

*Specific aims*:
(1)To compare the effects of n-3 PUFA supplementation, AEx training, and the combination of both on disease progression, cardiometabolic health, and quality of life in individuals with RA.(2)To compare the effects of n-3 PUFA supplementation, AEx, and the combination of both on the plasma and synovial fluid levels of the SPMs in individuals with RA.(3)To examine the relationship between the plasma levels of the n-3 PUFA derived SPMs with systemic disease progression, cardiometabolic health, and quality of life in individuals with RA

To achieve these aims we have designed a randomized, 16-week, placebo-controlled, blinded interventional trial.

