### Study design

This study consists of a 16-week intervention with n-3 PUFAs and/or aerobic exercise (AEx) training. The subjects will be randomly assigned in a double-blinded manner to one of four groups: placebo control (PLA), PLA+AEx, n-3, or n-3+AEx. A stratified randomized assignment (by block) process will be employed to ensure that the experimental groups are balanced for disease activity, pharmacological treatment, sex, and age. The principal investigator and pharmacy personal will be aware of patient allocation and will code the information. Patients and exercise intervention supervisors will be blinded for supplement intervention, while medical specialists and database analysis personal will be blinded for supplement treatment and exercise intervention. The study will be unblinded for patients and medical specialist if the participant worsens their condition according to the criteria described below or if they decide to drop out the study.

The training sessions will be conducted at the Laboratorio de Ciencias del Ejercicio en el Ciclo Vital (Lab-CERVITAL), Universidad de O’Higgins. The week before intervention the participants will perform RA specific tests (e.g., Disease Activity Score-28) and functional measurements (e.g., handgrip strength), peak aerobic capacity test, a dietary and physical activity assessment, and blood samples will be collected. Subsequently, participants will start their 16-week intervention (PLA, PLA+AEx, n-3, or n-3+AEx). At the end of the intervention the same initial measurements, questionnaires, and assessments will be collected. In a subgroup of participants (n=24 in total or n=6 per group) extraction of synovial fluid will be performed before and after the intervention.

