### Statistical analysis

Results will be expressed as mean ± SD. A two-way ANOVA with repeated measures followed by Fisher’s least significant difference post-test for multiple comparisons between groups will be used. Linear regression models will be constructed to examine the association between SPMs and clinical, functional, and health parameters, accounting for participant age, sex, and BMI as covariates. A value of p<0.05 will be considered statistically significant.

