## Discussion

RA is a chronic autoimmune and inflammatory disease characterized by inflammation around the joints leading to substantial damage of the cartilages, bones, tendons, and ligaments, significantly affecting overall function, quality of life, and increasing the propensity of mortality. The current treatments for patients with RA (DMARDs, NSAIDs, and anti-TNF biologics) intend to disrupt the inflammatory response and slow disease progression; however, their chronic consumption may lead to unwanted side effects (immunosuppression and infections) and prevent optimal resolution and tissue repair, which is imperative in RA. Further, the lack of robust and sensitive biomarkers to determine treatment responsiveness in RA has impeded proper tracing and development of novel individualized interventions. Therefore, elucidating the SPMs, as well as the underlying inflammatory and SPM synthesis transcriptional pathways, associated with the improvements in disease progression, cardiometabolic health, and quality of life after n-3 PUFA supplementation and AEx training could lead to the development of new markers and individualized treatment strategies that improve overall health and quality of life in RA individuals. Finally, these results could prompt the development of new pharmacological treatments that enhance the production of the SPMs observed after n-3 PUFA supplementation and AEx training to improve treatment outcomes in RA individuals.

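### The SPM-outcome regressions carry no treatment-arm term, so they can show an association for any SPM-outcome pair that treatment moves, even with no within-arm link

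*Protocol article*

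**What the plan says.** The Statistical analysis section of the protocol article gives one analysis for this question: "Linear regression models will be constructed to examine the association between SPMs and clinical, functional, and health parameters". The adjustment named for these models is limited to three participant characteristics: "accounting for participant age, sex, and BMI as covariates". The threshold is the general one: "A value of p<0.05 will be considered statistically significant". Participants are randomised to "placebo control (PLA), PLA+AEx, n-3, or n-3+AEx", a 2×2 layout of supplement and exercise.

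The regression serves specific aim 3: "To examine the relationship between the plasma levels of the n-3 PUFA derived SPMs with systemic disease progression", along with cardiometabolic health and quality of life. That aim treats people with RA as one population. The research hypothesis is that n-3 and exercise improve the outcomes and that "these changes will be associated with SPM production in blood and synovial fluid". The Abstract's conclusion reads the result mechanistically: "The study aims to elucidate the SPMs that regulate the inflammatory gene expression pathways". The Discussion hopes that the findings "could lead to the development of new markers and individualized treatment strategies".

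Nowhere does the article add arm to these models or plan them within arm.

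**The concern.** On the protocol's own premises, arm drives both sides of the regression. The Introduction describes SPMs as metabolites of n-3 fatty acids, and two of the four arms receive those fatty acids daily. The outcomes section chooses morning stiffness because n-3 is reported to improve it. The hypothesis has exercise acting on outcomes too, with SPMs as a possible explanation.

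If n-3 raises an SPM and also improves an outcome by some unrelated route, participants on n-3 will tend to have a high SPM and a good outcome, and those on placebo the reverse. Across arms the two are then correlated although neither affects the other. Age, sex and BMI cannot remove this. As baseline characteristics they are independent of arm by randomisation, and age and sex are also stratification factors.

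Aims 1 and 2 already compare the arms on outcomes and on SPMs. Aim 3 adds something only if it shows association beyond what arm explains. A slope that may simply restate the treatment contrast is weak ground for calling an SPM a marker or a mechanism.

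**Working it through.** The article gives no sample size, power or expected correlation for these regressions, so there is no figure to reproduce. The check asks how often the stated model finds an association when none exists within arms.

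**Inputs from the protocol**
- Four arms, 18 completers each: 4 × 18 = 72 (Sample size).
- Covariates age, sex and BMI; threshold 0.05, taken as two-sided.
- Effect size 0.42 (Sample size; metric not named).

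**Assumptions**
- dS, the n-3 effect on the SPM in within-arm SDs: 0.5, 1, 1.5 and 2. The documents give no value.
- dY, the n-3 effect on the outcome in within-arm SDs: 0.42 or 0.84. The second is 2 × 0.42. It is the two-level difference implied if 0.42 is Cohen's f and n-3 alone carries it. A one-way four-group ANOVA with f = 0.42 needs 17 per group (power 0.815; 0.840 at 18), close to the stated 18. A standardised two-group difference of 0.42 would need 89 per group.
- No link between SPM and outcome within any arm.

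**Induced correlation.** For two variables linked only through a 50/50 factor, with a better outcome being a lower value:

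r = −0.25·dS·dY / √[(1 + 0.25·dS²)(1 + 0.25·dY²)]

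- dS = 1, dY = 0.42: −0.105 / √(1.25 × 1.0441) = −0.09
- dS = 2, dY = 0.84: −0.42 / √(2 × 1.1764) = −0.27

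**False-positive rate.** Simulated trials, ordinary least squares of outcome on SPM, age, sex and BMI:

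| SPM shift (SD) | Outcome shift 0.42 SD | Outcome shift 0.84 SD |
|---|---|---|
| 0.5 | about 7% | about 11% |
| 1 | about 11% | about 31% |
| 1.5 | about 18% | about 50% |
| 2 | about 22% | about 65% |

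Repeat runs agree to within one or two percentage points.

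**Other settings**
- Either shift zero: the rate stays near 5%.
- All 88 participants retained, SPM shift 2 SD: 26% (outcome shift 0.42) and 73% (0.84).
- Exercise also moves both (0.5 SD on SPM, 0.42 SD on outcome, with n-3 at 1 and 0.42): about 20% with the stated covariates, 7% with n-3 alone added, 5% with n-3, exercise and their interaction.
- n-3 × exercise synergy on both (assumed 1–2 SD on SPM, 0.84–1.2 SD on outcome): main-effect arm terms alone leave 7–19%; adding the interaction restores about 5%.
- True within-arm slope of 0.3 (dS = 1, dY = 0.42): the fully arm-adjusted model still detects it in about 65% of trials.

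**The case against.** **Pooling and timing are inferred.** The article does not say that the arms are pooled, or whether baseline, week-16 or change values enter. Within-arm or baseline-only models would escape the problem, and a condensed article may leave such detail to another document. This stands as a limit on certainty. However, the covariate list is written out without arm, aim 3 treats participants as one population, and the hypothesis concerns changes during the intervention.

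**The size depends on assumed shifts.** This also stands. At an outcome shift of 0.42 SD the model gives no significant result in most trials, and at an SPM shift of 0.5 SD the excess is small. A reader might infer that SPMs are bound to test as associated with whatever n-3 improves. Only the expected correlation is non-zero; significance is not assured. Nor is every SPM-outcome pair affected, only those where treatment moves both.

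**Aim 3 asks for a relationship, not a within-arm slope.** For a marker of treatment response, variation produced by treatment is part of the signal, and no mediation analysis is promised. The marker sentence in the Discussion is a hope, and the randomised SPM comparison and the gene-expression data also bear on mechanism. So it would be too strong to say that the whole mechanistic conclusion rests on this model. The unadjusted slope may be reported as description, but alone it cannot separate an SPM link from a treatment effect by another route.

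**Conclusion.** The concern holds in a limited form. The stated covariates leave randomised arm as an uncontrolled common cause in the models serving aim 3, so an association can appear for any SPM-outcome pair that treatment moves, with no link inside the arms. With 72 completers the false-positive rate is about 7–22% at an outcome shift of 0.42 SD and about 11–65% at 0.84 SD, for SPM shifts of 0.5–2 SD. Full arm terms bring it back to about 5%.

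These figures rest on pooled arms, post-treatment or change values, a two-sided test and assumed SPM shifts. The primary comparison of morning stiffness is unaffected. The point should be corrected before aim 3 is analysed. Multiplicity across the SPM panel is a separate question, and the effect of omitting baseline values was not simulated.

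**What to change.** State which values the models use. For the plasma SPM models serving aim 3, regress the week-16 outcome on the week-16 SPM, adding n-3 arm, exercise arm, their interaction, baseline SPM and baseline outcome to age, sex and BMI. The interaction is needed because the hypothesis is one of synergy. Base any marker or mechanistic statement on the resulting within-arm slope, and label any model without arm terms as descriptive.

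The synovial subgroup has 24 people, 6 per arm. The full model has 10 coefficients including the intercept, leaving 24 − 10 = 14 residual degrees of freedom. Keep that model small, with arm terms taking priority, or treat it as descriptive.

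The cost is five more terms from data already collected, and slopes that will be smaller and less often significant. The within-arm slope is still observational, since SPM level is not randomised, and it does not prove mediation.

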### Characterization and anthropometric measures of participants

Body mass and height will be determined with a scale and wall-mounted stadiometer. The participant’s age, body mass index (BMI), educational status, socioeconomic level, years of diagnosis, smoking habits, comorbidities, and medications will be recorded.

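### The SPM–outcome regressions adjust only for age, sex and BMI; adding recorded baseline antirheumatic treatment would guard cheaply against plausible confounding

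*Protocol article*

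**What the plan says.** Specific aim 3 in the Introduction is "To examine the relationship between the plasma levels of the n-3 PUFA derived SPMs with systemic disease progression"; the aim also extends to quality of life and to cardiometabolic outcomes. The Statistical analysis section serves it with one sentence: "Linear regression models will be constructed to examine the association between SPMs and clinical, functional, and health parameters". The adjustment named in that sentence is given as "accounting for participant age, sex, and BMI as covariates". The covariate list is therefore stated and not left open.

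Elsewhere the article treats medication as important:

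- **Participants** admits patients taking NSAIDs, glucocorticoids or DMARDs under a stable-dose rule, without requiring a common regimen.
- **Study design** stratifies randomisation so that groups are "balanced for disease activity, pharmacological treatment, sex, and age".
- **Characterization and anthropometric measures of participants** states that "comorbidities, and medications will be recorded".
- **Introduction** says that these drugs improve function, including stiffness, and quality of life.
- **Discussion** names DMARDs, NSAIDs and anti-TNF biologics and says that "their chronic consumption may lead to unwanted side effects (immunosuppression and infections) and prevent optimal resolution and tissue repair".

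Medication is not among the covariates of the SPM regressions.

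**The concern.** Stratified randomisation balances drug use between the four arms. It does not balance drug use between patients with high and low SPM levels, and that is the contrast aim 3 examines. If treated patients differ from untreated patients in both SPM level and outcome, the fitted SPM slope carries part of that difference. Putting study arm in the model would not remove it, because the difference exists within each arm.

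The bias can go either way. If drug users have lower SPMs and fewer symptoms, a real protective slope is masked. If drug users have lower SPMs and more symptoms, because sicker patients are treated more heavily, an inert SPM looks protective. The Discussion hopes to draw new markers, individualised strategies and new drug treatments from these associations, so a drug-use artefact could be read as a mechanism.

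**Working it through.** **Inputs from the article.** Minimum 18 per group × 4 = 72; recruited 22 × 4 = 88; after 20% dropout, 88 × 0.80 = 70.4, so about 70. The article gives no figure for the regressions. Its sample size reproduces if 0.42 is read as Cohen's f in a four-group one-way ANOVA (17 per group for 80% power, against the stated 18), but this has no bearing on the present point.

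**Assumptions not in the article.** A proportion p of patients uses the drug (D = 1). SPM level is S = aD + error and outcome is Y = βS + bD + error, with unit residual SDs. Three unrelated covariates stand in for age, sex and BMI.

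**Bias when D is omitted:** ab·p(1−p) / [1 + a²·p(1−p)].

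With p = 0.5 and β = 0:
- a = −0.3, b = 0.3: −0.0225/1.0225 = −0.022
- a = −0.5, b = 0.5: −0.0625/1.0625 = −0.059
- a = −0.8, b = 0.8: −0.16/1.16 = −0.138
- a = −1.0, b = 1.0: −0.25/1.25 = −0.20

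With equal shifts these values are also the S–Y correlations r. The approximate test statistic is r√n/√(1−r²). At n = 70 and 1.0 SD it is 0.20 × 8.367/0.980 = 1.71. Against a critical value of about 2.00, the rejection probability is about 0.39. At 0.8 SD the statistic is 1.165 and the probability about 0.20.

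**False-positive rate per SPM, true slope zero (simulation, 4,000 or 8,000 runs per setting):**

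| Shift in SPM / outcome (SD) | Users | n | Stated covariates | Drug added |
|---|---|---|---|---|
| 0.3 / 0.3 | 50% | 72 | 5.6% | 4.8% |
| 0.5 / 0.5 | 50% | 70 | 7.5% | 4.9% |
| 0.8 / 0.8 | 50% | 70 | 20% | 4.8% |
| 1.0 / 1.0 | 50% | 70 | 38% | 5.0% |
| 0.8 / 0.2 | 50% | 70 | 6.0% | not run |
| 0.8 / 0.3 | 50% | 70 | 7.5% | not run |
| 0.5 / 0.5 | 80% | 70 | 5.9% | not run |
| 0.8 / 0.8 | 90% | 70 | 7.6% | not run |

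At n = 88 the 0.3, 0.5 and 0.8 SD rows with 50% users give about 5%, 8% and 24%.

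**Adding arm instead of drug** (n = 70, drug independent of arm): 6.9%, 20% and 36% at 0.5, 0.8 and 1.0 SD, so it does not help.

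**Masking.** Take β = −0.30, the drug lowering both variables by 0.8 SD, n = 72. The expected slope is −0.30 + 0.138 = −0.162. Simulation gives −0.163 with power 0.26 when the drug is omitted, and −0.303 with power 0.68 when it is included. At 0.5 SD the slope is −0.241 and power 0.50, against 0.67 with the drug included.

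**Change regressed on change.** With the same drug shift at both visits it cancels: 5.3% and 5.2% false positives at 0.8 and 1.0 SD without the drug in the model.

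**Cost of adjustment.** For a partial correlation of 0.30 at n = 72, power goes from 0.749 to 0.748 with four added terms and to 0.747 with seven.

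**The case against.** A reader might infer that the article's own reasoning makes treatment a common cause of SPM level and outcome. The text does not go that far. The Discussion says only that chronic use may "prevent optimal resolution and tissue repair, which is imperative in RA". It does not say that the drugs change plasma SPM concentration, which is the predictor, and glucocorticoids are not in its list. The step from impaired resolution to lower SPM level is inference. This objection stands: treatment is a plausible confounder, not a documented one.

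A reader might also take 20% or 38% as the expected error rate. Those rates need shifts of 0.8 to 1.0 SD on both variables and near-equal numbers of users and non-users. Milder or less even settings give about 5–8%. This stands too.

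The design narrows the problem. Entry is limited to moderate disease activity and drug doses must stay constant. The hypothesis speaks of changes, and a constant drug effect cancels in a change-on-change model. But the Statistical analysis section does not say whether levels or changes are regressed, and aim 3 speaks of plasma levels. Constant doses also limit variation within a patient, not between patients.

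Finally, covariate lists are often extended in a later analysis plan. That would answer a silent article; this one names its list.

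**Conclusion.** The point holds as a cheap improvement to a non-primary, associational analysis. The stated models leave out a plausible confounder that varies between participants, is a stratification factor and is already recorded. The size of the bias cannot be derived from the document. The range above, from negligible to about 38% false positives per SPM, rests on assumed user proportions and assumed drug effects. The return to about 5% after adjustment also depends on the simulated confounder being a simple yes/no variable; in practice an indicator misses dose and specific agent, so some confounding may remain. The randomised comparison of morning stiffness is not affected.

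**What to change.** In the Statistical analysis section, extend the covariates of the SPM regressions as follows:

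- Add baseline treatment class as yes/no indicators: NSAID, glucocorticoid, DMARD/biologic. The article does not define its stratification categories, so the classes should be written out.
- Where the outcome is a post-intervention value, also add its baseline value. This does not apply to a baseline cross-sectional model.
- In the model for analgesic use, omit the baseline NSAID indicator if baseline analgesic use is already included, since the two largely duplicate each other.
- Use on-study NSAID use only in a sensitivity analysis, because it may lie on the causal path.

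The cost is wording and about three to four degrees of freedom out of roughly 70 to 88 patients, with almost no loss of power. Medications are already recorded and the outcomes are already measured before the intervention.

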### Sample size

The sample size calculation for this study is based on an α level of 0.05, a power (1-β) of 0.8, and effect size of 0.42 (morning stiffness).
^
11
^ A minimum of 18 participants are necessary per group; however, 22 individuals will be recruited to account for a typical dropout rate of 20% in long-term intervention studies.

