### Primary and secondary outcomes

Primary outcome: Early morning stiffness is one of the main outcomes significantly improved by n-3 PUFA supplementation in RA patients.
^
11
^ Therefore, the difference in the duration (minutes) of early morning stiffness has been selected as the primary outcome to compare the intervention effect in each group after the intervention period.

Secondary outcomes: Other relevant outcomes which allow the assessment of disease progression will be measured, such as the Disease Activity Score-28, DHA-SPMs, tender and swollen joint count, quality of life, grip strength, analgesic use, and TNF-α blood levels.

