### Leukocyte gene expression

cDNA will be prepared by reverse transcription of 1 ug of total RNA, using the SensiFASTTM cDNA Synthesis Kit (Bioline) according to manufacturer’s protocol. RNA quantity and quality will be assessed using a Nanodrop 8000 (ThermoScientific, Wilmington, DE, USA) and an Agilent 2100 BioAnalyzer (Agilent Technologies Inc., Santa Clara, California, USA), respectively. Real-time RT-qPCR will be carried out to quantify the changes in the expression of genes associated with inflammatory pathways and SPM synthesis, including TNF-α, interleukin-1β (IL-1β), IL-6, cyclooxygenase-2 (COX-2), lipoxygenase-5 (ALOX5), lipooxygenase-12 (ALOX12), lipooxygenase-15 (ALOX15), and calcium-independent phospholipase A2 VIA (iPLA2VIA). 18S ribosomal RNA (18SRNA) and glyceraldehyde 3-phosphate dehydrogenase (GAPDH) will be used as housekeeping genes. Data will be analyzed using the ΔΔCt method.

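### One unadjusted p<0.05 rule covers the secondary outcomes, SPM panel, genes and SPM regressions, though the trial aims to single out the responsible SPMs and pathways

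*Protocol article*

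**What the plan says.** The Statistical analysis section of the protocol article names a two-way repeated-measures ANOVA, then Fisher's "least significant difference post-test for multiple comparisons between groups will be used". It adds linear regressions relating SPMs to clinical and functional measures, adjusted for age, sex and BMI. It closes with a single criterion: "A value of p<0.05 will be considered statistically significant". It gives no adjustment across endpoints or markers.

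The rule has to cover:

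- **Groups:** "one of four groups: placebo control (PLA), PLA+AEx, n-3, or n-3+AEx" (Study design), which makes six pairs per endpoint.
- **Secondary outcomes:** "such as the Disease Activity Score-28, DHA-SPMs, tender and swollen joint count, quality of life, grip strength, analgesic use, and TNF-α blood levels" (Primary and secondary outcomes). That is seven items, and the wording leaves the list open.
- **Genes:** RT-qPCR "to quantify the changes in the expression of genes associated with inflammatory pathways and SPM synthesis" (Leukocyte gene expression), with eight genes named, again as an open list.
- **SPMs:** an oxylipin panel in plasma and synovial fluid, with no number of analytes given (Analyses of SPMs).
- **Regressions:** SPMs against clinical measures, the third specific aim in the Introduction.

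The purpose is one of selection: "The study aims to elucidate the SPMs that regulate the inflammatory gene expression pathways" (Abstract). The Discussion hopes that the results will yield markers and tailored treatment. No section calls the secondary, SPM or gene results exploratory.

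**The concern.** Picking responders out of a panel is a selection problem. A 5% error rate per test limits how often each null marker is wrongly called. It does not limit what share of the called markers is wrong. LSD adds no protection across endpoints. Within an endpoint it tests each pair at an unadjusted 5%, so its description as the step for multiple comparisons may give false comfort.

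At stake is whether an SPM, gene or secondary outcome reported as significant can be taken as evidence of mechanism or as a candidate biomarker.

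**Working it through.** **The plan's own figures.** The protocol states no family-wise or false discovery rate. Its only error figure is alpha 0.05 in Sample size, attached to morning stiffness: "A minimum of 18 participants are necessary per group". Reading the effect size of 0.42 as Cohen's f (the metric is not stated), a one-way ANOVA on four groups needs 17 per group for 80% power (power 0.815) and has power 0.840 at 18. So 18 is reproduced to within one patient. The calculation concerns one outcome and makes no allowance for the others.

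**Inputs.** Four groups of 18 evaluable patients (72 in total). Seven named secondaries, counting tender and swollen joints as one item and DHA-SPMs as one test. Eight named genes. Two-sided 5% tests. With one measurement before and one after, the group-by-time test equals a one-way ANOVA on the changes, so one overall F test per endpoint is used.

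**Step 1: independent endpoints, nothing differs.** Chance of at least one false positive = 1 - 0.95^m.

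- Seven secondaries: 1 - 0.95^7 = 30%
- Eight genes: 1 - 0.95^8 = 34%
- Both, m = 15: 1 - 0.95^15 = 54%; expected number 15 x 0.05 = 0.75

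**Step 2: correlated endpoints.** Independence cannot hold exactly, because DAS28 contains the joint counts (RA disease progression). The correlations are assumptions. Simulating 15 endpoints under the global null (4,000 trials, standard error about 0.008):

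| Common correlation | At least one significant F among 15 |
|---|---|
| 0 (formula) | 54% |
| 0.3 | 48% |
| 0.5 | 39% |
| 0.8 | 22% |

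The expected number stays at 0.75 whatever the correlation.

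**Step 3: what LSD changes.** If pairs are examined only after a significant F, the table stands when nothing differs. If one group truly differs, the F test no longer protects the rest: LSD then has a 12% error rate among the other three equal groups. If pairs are read without requiring a significant F, one endpoint alone carries about 20%.

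**Step 4: the regressions.** The numbers of SPMs and outcomes are not given, so a range is assumed: 1 to 10 SPMs against 10 outcomes, 72 patients, three covariates, no true association.

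| SPMs (x 10 outcomes) | Correlation 0 | Correlation 0.5 |
|---|---|---|
| 1 | 39% | 28% |
| 3 | 78% | 59% |
| 5 | 92% | 73% |
| 10 | 99% | 90% |

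For 3 SPMs the independent formula agrees: 1 - 0.95^30 = 79%.

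**The case against.** **This is a condensed article, and an analysis plan may exist.** Handling of secondary and biomarker multiplicity is often left to that plan, and a 0.05 threshold is compatible with adjusted p-values. This has force against any complaint of mere silence. But the article does fix a rule: it names LSD as its multiple-comparison step, places every analysis in the section under one threshold, and makes marker identification an aim. That rule suits the aim badly as stated.

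**There is a hierarchy.** One primary outcome is named, and the sample size is tied to it. This stands: the choice among endpoints cannot inflate the primary claim. Whether LSD is adequate within the primary outcome is a separate question.

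**The global null is a worst case.** The trial rests on n-3 supplying the substrate for DHA-derived SPMs, so some SPM tests are probably not null. The Discussion is also hedged about what the results could lead to. Both points stand and limit the size of the concern.

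**Stronger readings that the documents do not support.**

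- A reader might infer that a false significant marker is more likely than not among the named endpoints. That requires near-independence; at correlations of 0.3 and 0.5 the chance is below one half. A figure of 56% would also need 16 tests, which means counting the two joint counts separately.
- A reader might multiply eight genes by six pairs and expect 48 x 0.05 = 2.4 false gene findings. The protocol places LSD after the ANOVA. If a significant F is required, simulation gives about 0.9 expected false pairs across the eight genes when nothing differs.

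**Conclusion.** The point holds for the secondary and mechanistic claims. The stated rule gives roughly a 39-54% chance of at least one false positive across the 15 named secondaries and genes, for correlations from 0.5 to 0, assuming one overall test each and no true differences. Stronger correlation lowers it (22% at 0.8). Further SPM analytes and the regressions raise it; the regressions may be the largest source, at 59-78% for an assumed 3 SPMs by 10 outcomes. The SPM count, the outcome count and the correlations are assumptions, and true effects would reduce the number of null tests.

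This should be changed, but it does not threaten the main conclusion on morning stiffness.

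**What to change.** 1. Keep p<0.05, without adjustment across endpoints, for the single primary outcome.
2. Define four marker families: plasma SPMs, synovial SPMs, genes, and the SPM-by-outcome regressions. List their members before analysis, including the SPM analytes and the outcomes entering the regressions.
3. Apply Benjamini-Hochberg control at a 5% false discovery rate within each family. For the SPM and gene families use either the overall group-by-time test per marker or the n-3, AEx and interaction effects of the 2x2 design. In the second case all three p-values per marker enter the family (8 genes x 3 = 24 tests). For the regressions use the SPM coefficients.
4. Report the remaining secondary outcomes with 95% confidence intervals and label them exploratory.

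If no gene truly differs, the chance of calling any gene falls from about 34% (one independent test each) to about 5%. Across four families it would be about 1 - 0.95^4 = 19% if the families were independent and nothing differed.

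The cost is a few sentences and fixed lists, with no extra patients or assays. Some markers with p just below 0.05 will no longer be called significant. With eight genes and one test each, a lone signal must reach 0.05/8 = 0.00625. The loss will be felt most in synovial fluid, which is sampled in only 24 patients, six per group.
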